### Interventions

#### Usual-Care

Patients in the usual-care arm will continue with the treatment plan and appointments decided upon with their clinician prior to enrolling in the study (see Figure 1). According to the clinic’s current practice, a clinician reviews the patient’s fasting blood glucose log during appointments and titrates the insulin dose. Our research assistant (RA) will collect data, such as fasting blood glucose readings, insulin dosage adjustments, and appointment duration, from patients after appointments, in-person or by phone, as well as appointment duration from clinicians. These patients will continue to visit their primary care providers and have routine HbA1c tests according to the standard of care.

**Figure 1 figure1:**
[figure not shown]
Usual-care flowchart.

#### Mobile Insulin Titration Intervention

Patients in the MITI arm will sign up for a Web-based health management platform in the clinic with the assistance of the research staff. The platform allows patients and clinicians to communicate via text messaging. Patients will receive a text message each weekday from the platform requesting the patient’ s fasting blood glucose level for that day. The messages will be automatically delivered each morning at a time prespecified by the patient, in either English or Spanish. Patients will respond via text message with their fasting blood glucose levels. Mobile phones can be provided to any patient who is otherwise eligible but does not have a mobile phone. It is implicit that a patient must be able to operate a mobile phone to participate in the study.

The diabetes nurse educator will check patients’ responses on the secure Web portal each weekday and call any patient reporting alarm values (ie, a blood glucose level <80 mg/dL or >400 mg/dL). Each Thursday afternoon, the diabetes nurse educator will call the patients to adjust their insulin dose according to a titration algorithm developed by physicians and nurses on the study team. The diabetes nurse educator may leave a voicemail with insulin titration instructions. If the patient cannot be contacted by phone, the diabetes nurse educator may call the patient’s emergency contact upon her discretion. Another clinician may check text responses and make titration phone calls if the diabetes nurse educator is not available. If Thursday is a holiday, the titration calls can take place on another weekday.

This protocol of weekday text messages and weekly phone calls will continue for up to 12 weeks (see Figure 2), until the patient reaches their optimal insulin dose, or the patient chooses to withdraw from the study. Patients may attend appointments with their primary care provider during the intervention, but will not need to attend appointments specifically for diabetes management (eg, high HbA1c clinic or diabetes nurse educator appointments) within the primary care clinic. After completing the protocol, the patient will be transferred back to usual care in the clinic. The research team will arrange for follow-up appointments with the patient’s primary care provider and, if appropriate, appointments with the diabetes nurse educator or high HbA1c clinic, so that the patient can resume their diabetes care through standard clinic visits.

**Figure 2 figure2:**
[figure not shown]
Intervention (MITI) flowchart.

#### Follow-Up

Patients in both arms will be contacted by the RA at approximately 12 weeks in the study to remind them of their routine HbA1c test. The RA will also arrange to administer the Diabetes Treatment Satisfaction Questionnaire, either when the patient is present in the clinic for their blood test or via phone.

### Implementation Challenges

During this pilot study, we refined our technological approach because our initial health management platform could not send text messages to prepaid mobile phones. Patients who had prepaid mobile phones either continued to attend in-person clinic appointments for insulin titration or were provided a mobile phone to use for the duration of the study. We resolved this issue in 2014 when we switched to a different health management platform that could send text messages to any mobile phone.

Prior to May 2014, patients were stratified by whether the patient was initiating insulin therapy or having their existing insulin dose titrated, and by HbA1c level (8-11% or >11%). We removed the HbA1c stratification after finding that not all patients had an HbA1c value available in their medical record at the time of enrollment.

### Intervention Standardization and Fidelity

To ensure that all patients receive the same level of care during the intervention, the diabetes nurse educator will use a script outlining what must be covered during an insulin titration phone call. The nurse will also use scripts to leave titration instructions via voicemail and for speaking with, and leaving voicemails for, the patient’s emergency contact. These scripts were implemented in May 2014. The nurse can consult the principal investigator in real time if any event arises with a patient that is not outlined in the study protocol.

### Sample Size (Power Analysis)

Our sample size is based on the hypothesis that the proportion of patients in the MITI group who reach their optimal insulin dose within 12 weeks will be significantly greater that the proportion of patients in the usual-care group who reach this goal. Based on the experience of clinicians treating our patient population at our study site, we expect that, at most, 50% of patients in the usual-care arm will reach their optimal insulin dose by 12 weeks. We expect at least 80% of patients in the MITI arm to reach this goal, since this arm will have weekly insulin titration phone calls, and frequent titration is associated with improved glycemic control [10,21,22]. Using Fisher's exact test with a 2-sided type I error rate of 5% to achieve at least 80% power, we need 44 subjects per group to detect a difference of 30% between 80% and 50%. Assuming a 10% drop-out rate by week 12, we need a total of 98 patients (49 per group).

### Recruitment, Randomization, and Retention

We will recruit patients from the Adult Primary Care Center. Clinicians can alert the research study staff of any patient who is interested in the study and may be eligible (see Figure 3). The RA will also review the clinic’s electronic medical records to identify patients that may be eligible for the study. The RA will screen the patient for eligibility, explain the study, and provide them with a consent form to read and sign in person at the Adult Primary Care Center. All patients must provide informed consent before participating in the study protocol.

Since patients will be randomized sequentially at the time they provide informed consent, we will use block randomization (block size of 4) to make sure the number of patients in each arm is approximately balanced at any time point during the study. Patients will be stratified by whether the patient is initiating insulin therapy or having their existing insulin dose titrated. The random allocation sequence will be computer-generated by a coinvestigator and concealed in presealed envelopes. The patient’s arm assignment will be revealed to the patient and research team at the time of study enrollment by the RA. The research team and clinicians will not be blinded since the intervention requires that they alter the patient’s treatment plan or, in the case of the usual-care arm, collect data from clinicians and patients regarding their appointments.

At the time of enrollment, patients will receive a US $10 MetroCard to be used for travel to and from the clinic. Patients will receive a glucometer and a supply of test strips to ensure that they can test their blood glucose levels for the duration of the study. At approximately 12 weeks into the study, the research assistant will contact patients by phone to remind them to return to the clinic for their 3-month HbA1c blood test and complete the satisfaction questionnaire. Patients will receive an additional US $10 MetroCard.

**Figure 3 figure3:**
[figure not shown]
Enrollment flowchart.

### Data Monitoring

A data and safety monitoring board is designated to meet quarterly, or sooner if necessary, to discuss any potential safety issues. In particular, the study team and the board will review any cases of hypoglycemia or hyperglycemia that occur among our patients (to assess the safety of our titration algorithm) and our ability to reach patients by phone (to ensure that our patients are being monitored regularly during the intervention).

### Data Analysis

First, we will summarize all the baseline and follow-up measures using means and standard deviation (SD), medians and interquartile range (IQR), or frequencies, and then compare them between the two arms. Second, we will test if baseline characteristics (eg, demographic measures and baseline HbA1c levels) are balanced between the two randomized arms. Third, to evaluate the intervention effects, we will use the chi-square test or Fisher’s exact test for categorical outcomes (eg, whether or not a patient reaches optimal dose), Student’s *t* test or Wilcoxon rank-sum test for continuous outcomes (eg, change in HbA1c levels, rate of hypoglycemia, scores on the Diabetes Treatment Satisfaction Questionnaire, number and duration of titration appointments, and patient health care utilization), and log-rank test for time to reach optimal dose. Fourth, we will conduct multiple linear regression analyses for continuous outcomes and multiple logistic regression analyses for categorical outcomes to further evaluate the intervention effects, adjusting for some baseline characteristics and/or their interactions with the treatment assignment. At this stage, we will conduct multiple imputation to deal with the missing data problem. Finally, we will conduct descriptive analyses for other secondary outcomes, such as feasibility outcomes, patient travel time and waiting room time, and patient co-pays. We will also review the content of semistructured interviews to identify common themes in patient feedback.

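### Randomisation is stratified by insulin initiation versus titration, but the primary chi-square/Fisher test and the log-rank test ignore that stratum: both stay valid, but forgo some power if it is prognostic

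*Protocol article*

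**What the plan says.** On allocation, the section on recruitment and randomisation uses blocks of 4 and states: "Patients will be stratified by whether the patient is initiating insulin therapy or having their existing insulin dose titrated". The Implementation Challenges section adds that before May 2014 "patients were stratified by whether the patient was initiating insulin therapy or having their existing insulin dose titrated, and by HbA1c level". The HbA1c factor was then dropped because some patients had no value on record at enrolment. Initiation versus titration is therefore the one factor in force for every patient.

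On analysis, the Data Analysis section evaluates the intervention with the chi-square or Fisher's "exact test for categorical outcomes (eg, whether or not a patient reaches optimal dose" and with a log-rank test for time to that dose. No stratum is named for either. A later step fits linear and logistic regressions "adjusting for some baseline characteristics and/or their interactions with the treatment assignment". It does not name the randomisation factor, and no regression for time to event is mentioned.

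On sample size, the calculation uses the same unstratified Fisher's "exact test with a 2-sided type I error rate of 5% to achieve at least 80% power". It assumes that "at most, 50% of patients in the usual-care arm will reach their optimal insulin dose by 12 weeks", and for the other arm: "We expect at least 80% of patients in the MITI arm to reach this goal".

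**The concern.** Stratified blocks force the arms to be nearly balanced within each stratum. If the stratum predicts who reaches the optimal dose, that balance removes a source of chance difference between the arms. An unstratified test still counts the between-stratum variation as noise. Its standard error is then too large, its true type I error falls below 5%, and some real effects that a stratified test would detect are missed.

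What is at stake is efficiency and consistency with the design, not a false positive. The article's Discussion itself expects the small sample to limit power, so power that can be had by wording alone is worth taking. The log-rank test deserves more attention than the primary test, because the plan gives it no adjusted counterpart.

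**Working it through.** **1. The plan's own figure.** Inputs from the Sample Size section: 50% versus 80%, two-sided 5%, Fisher's exact test, at least 80% power, 10% drop-out. Enumerating all pairs of binomial outcomes gives power of 79.6% at 43 per group and 80.2% at 44, so 44 is reproduced. Drop-out: 44 / 0.90 = 48.9, rounded up to 49 per group, 98 in total. This also agrees.

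**2. Why ignoring the stratum is conservative.** With arms balanced within strata, the Pearson and Cochran-Mantel-Haenszel (CMH) statistics compare the same observed and expected counts. They differ in the variance: about p(1 − p) at the pooled rate p for Pearson, and the average of p_h(1 − p_h) over strata h for CMH. Example under the null, two equal strata with rates of 30% and 70%:
- pooled: 0.5 × 0.5 = 0.25
- within strata: (0.3 × 0.7 + 0.7 × 0.3) / 2 = 0.21
- ratio: 0.21 / 0.25 = 0.84

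Pearson's type I error at 44 per arm falls from 4.4% (no stratum effect, both arms 50%) to 2.8%. With equal stratum rates the ratio is 1 and nothing is lost.

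**3. Size for the primary test.** The documents give neither the stratum split nor stratum-specific rates, so both are assumed: a 50:50 split, 44 per arm balanced within strata, marginal rates held at 50% and 80% (65% in both arms under the null), 40,000 replicates, Monte Carlo error about 0.1 to 0.2 points. Like is compared with like: asymptotic with asymptotic, exact with exact.

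| Between-stratum odds ratio | Power, Pearson → CMH | Power, Fisher → exact CMH | Type I error, Pearson | Type I error, Fisher |
|---|---|---|---|---|
| 1 | 86.0 → 85.2% | 79.8 → 80.0% | 5.2% | 2.9% |
| 2 | 86.7 → 86.5% | 80.7 → 81.4% | 5.1% | 2.8% |
| 3 | 86.9 → 87.5% | 80.9 → 82.3% | 4.9% | 2.6% |
| 5 | 87.9 → 89.4% | 81.6 → 84.4% | 3.9% | 2.1% |
| 10 | 89.3 → 92.6% | 83.5 → 88.8% | 3.0% | 1.4% |

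The loss is the difference within a cell. At odds ratio 3 it is 0.6 (asymptotic) and 1.4 points (exact); at 5, 1.5 and 2.8; at 10, 3.3 and 5.3. A 30:70 split gives nearly the same.

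**4. Size for the log-rank test.** Assumptions: exponential times with 12-week hazards from the planned rates (−ln 0.5 / 12 and −ln 0.2 / 12), multiplied or divided by the square root of the between-stratum hazard ratio; weekly assessment in both arms; censoring at 12 weeks; 2,000 replicates. Monte Carlo error is 0.7 to 1.0 points for power and about 0.5 for type I error. Marginal rates are not held fixed, so only comparisons within a row are meaningful.

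| Between-stratum hazard ratio | Power, log-rank → stratified log-rank | Loss, points |
|---|---|---|
| 1 | 88.7 → 88.5% | none |
| 1.5 | 87.3 → 87.7% | 0.4 |
| 2 | 84.0 → 86.8% | 2.8 |
| 3 | 80.8 → 88.2% | 7.4 |
| 5 | 68.7 → 86.2% | 17.5 |

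The type I error of the unstratified log-rank test goes from 5.4% at hazard ratio 1 to 1.7% at 5.

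**The case against.** The strongest reply is that nothing is broken. The trial is sized on the test it names, that test reaches its 80%, and its type I error is never inflated by ignoring the strata. The study is a pilot. The planned logistic regression can include the stratum. All of this stands, and it makes the point one of efficiency.

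The reply also disposes of several stronger readings that a reader might infer:

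- **That stratifying would gain about 7 points.** With assumed stratum rates of 35%/65% (usual care) and 70%/90% (MITI), an asymptotic CMH test has 88.2% power and Fisher 81.1%. Most of that gap is asymptotic against exact testing. Like for like, CMH against Pearson is 88.2% against 87.2%, and continuity-corrected CMH against Fisher is 82.6% against 81.1%. With milder rates of 40%/60% and 73.5%/86.5%, CMH and Pearson are level (86.8% and 86.7%).
- **That Fisher's low type I error shows the harm.** At 44 per arm with no stratum effect, its size is already about 2.5 to 3%, from discreteness alone.
- **That the factor was chosen because it predicts the outcome.** The article gives a reason for blocking but none for the choice of stratifier.
- **That baseline tests will pick the covariates.** The Data Analysis section does not say so. The covariate list and the choice of interactions are detail that an article may leave to the full protocol or the SAP, neither of which is shown.

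The reply does not remove the mismatch. The article states the tests rather than leaving them open, and neither uses the stratum. The regression comes after the main test and does not name the factor, and time to optimal dose has no adjusted analysis at all.

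**Conclusion.** The point holds as a modest one. The primary and log-rank tests do not reflect the stratified allocation. Both are valid, and the 80% power claim at 44 per group is correct for the unstratified Fisher test. What is forgone depends on how prognostic initiation versus titration is, which the documents do not state. For the primary test the loss is 0 to about 1.5 points up to an odds ratio of 3, and reaches about 3 to 5 points only at the extreme value of 10. For the secondary time-to-dose comparison it could matter: negligible up to a hazard ratio of 1.5, but about 3, 7 and 18 points at 2, 3 and 5. These figures rest on the assumed splits, stratum effects and exponential times shown above. It would be wrong to conclude that the primary result would be unreliable or that the trial is underpowered for its stated assumptions.

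**What to change.** In the Data Analysis section, before any comparison of outcomes by arm:

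1. Make the primary test a CMH test stratified by initiation versus titration, in its exact version if an exact test is wanted, and report the Mantel-Haenszel risk difference with its 95% confidence interval.
2. Use a log-rank test stratified by the same factor for time to optimal dose.
3. Include the stratum as a main effect in the planned logistic regression.
4. State in a sentence how the HbA1c factor used before May 2014 is handled. It need not enter the primary test, since it was not in force throughout and some values were missing at enrolment.

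The cost is wording only, because the stratum is needed to randomise each patient and so is already known. If the stratum turns out not to be prognostic, the asymptotic version gives up 0.8 points (86.0% to 85.2%), and the exact version gives up nothing measurable (79.8% against 80.0%). The sample size need not change.

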**Methods:**

This is a pilot study evaluating an approach to insulin titration using text messages and phone calls among patients with insulin-dependent type 2 diabetes in the outpatient medical clinic of Bellevue Hospital Center, a safety-net hospital in New York City. Patients will be randomized in a 1:1 ratio to either the MITI arm (texting/phone call intervention) or the usual-care arm (in-person clinic visits). Using a Web-based platform, weekday text messages will be sent to patients in the MITI arm, asking them to text back their fasting blood glucose values. In addition to daily reviews for alarm values, a clinician will rereview the texted values weekly, consult our physician-approved titration algorithm, and call the patients with advice on how to adjust their insulin dose. The primary outcome will be whether or not a patient reaches his/her optimal dose of insulin glargine within 12 weeks.

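### The primary test of optimal-dose attainment ignores the initiating/titrating stratum used in the randomisation; if that stratum predicts attainment, a modest gain in power is forgone

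*Protocol article*

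**What the plan says.** In the protocol article, Recruitment, Randomization, and Retention describes "block randomization (block size of 4") and then: "Patients will be stratified by whether the patient is initiating insulin therapy or having their existing insulin dose titrated". Implementation Challenges shows that the same factor was in force from the start: "Prior to May 2014, patients were stratified by whether the patient was initiating insulin therapy or having their existing insulin dose titrated", at that time together with HbA1c level. Only the second factor was dropped: "We removed the HbA1c stratification after finding that not all patients had an HbA1c value available". Initiating versus titrating was therefore a stratification factor for the whole trial.

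Data Analysis evaluates the intervention with a chi-square test or Fisher's "exact test for categorical outcomes (eg, whether or not a patient reaches optimal dose"). It mentions no stratum. Sample Size (Power Analysis) uses the same unstratified Fisher test. A later step adds logistic and linear regression, "adjusting for some baseline characteristics and/or their interactions with the treatment assignment", to evaluate the effects further. The characteristics are not named.

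**The concern.** Blocking within strata keeps the arms balanced on the stratum, so differences between strata add almost nothing to the sampling error of the treatment comparison. A pooled two-by-two test does not know this and still counts those differences as error. If patients starting glargine reach the endpoint at a different rate from those already on a dose, the pooled test uses too large a variance. Its true type I error rate then falls further below 5%, and it detects a real effect slightly less often than a test that conditions on the strata.

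What is at stake is efficiency and calibration in a trial of 98 patients whose Discussion already concedes limited power. The stratum must be known for every patient before the envelope is opened, so using it in the analysis raises no missing-data problem of the kind that led to HbA1c being dropped.

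**Working it through.** **Inputs from the article.** Usual-care rate 50%, MITI rate 80%, two-sided 5%, Fisher's exact test, at least 80% power, 44 evaluable per group, 10% dropout, 98 in total (Sample Size). Allocation is 1:1 (abstract, Methods).

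**Reproducing the plan's figure.** Power = Σ Pr(X = x) Pr(Y = y) over all tables with Fisher p ≤ 0.05, where X ~ Bin(n, 0.8) and Y ~ Bin(n, 0.5). This gives 79.6% at n = 43 and 80.2% at n = 44. Then 44 / 0.9 = 48.9, so 49 per arm and 98 in total. The stated figures reproduce. The 80.2% is calculated; the article states only the 80% target.

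**Assumptions, because the article is silent.** Two equal strata (22 + 22 per arm), exact 1:1 balance within each, overall rates held at 80% and 50%, and a common odds ratio. The stratum gap d is the difference between the two strata's usual-care rates. Example for d = 40 points: usual-care rates 70% and 30%. An odds ratio of 4.95 turns these into 92% and 68%, which average 80%.

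**Variance argument.** With stratum share w and overall rate p, the ratio of within-stratum to pooled variance is 1 − w(1 − w)d² / [p(1 − p)]. For w = 0.5 and p = 0.5 this is 1 − d²: 0.96, 0.91 and 0.84 at gaps of 20, 30 and 40 points. The pooled test overstates the variance accordingly.

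**Exact enumeration.** For pooled Fisher, each arm's count is the sum of two binomials, and all tables with p ≤ 0.05 are summed. For the stratified exact test, condition on each stratum's total number of successes. The null distribution of the MITI count is then the convolution of two hypergeometric distributions, and the two-sided p sums all outcomes no more likely than the one observed. True size is evaluated at a null rate of 50% overall.

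| Gap (points) | Size, pooled Fisher | Size, stratified exact | Power, pooled Fisher | Power, stratified exact | Gain (points) |
|---|---|---|---|---|---|
| 0 | 2.6% | 2.7% | 80.2% | 80.4% | 0.2 |
| 20 | 2.3% | 3.1% | 80.6% | 81.6% | 0.9 |
| 30 | 1.9% | 3.1% | 81.1% | 82.9% | 1.7 |
| 40 | 1.5% | 2.9% | 81.9% | 85.0% | 3.1 |

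(Gains are taken before rounding.) Fisher's 2.6% with identical strata comes from discreteness alone. Pooling accounts only for the further fall, to 1.5% at a 40-point gap: about 1.1 of the 3.5 points by which the size then lies below 5%.

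**Unequal strata.** With 11 + 33 per arm and the smaller stratum having the higher rate, the same enumeration gives 80.5% vs 81.2%, 80.8% vs 82.0% and 81.3% vs 83.1% at gaps of 20, 30 and 40 points. These are gains of 0.7, 1.2 and 1.8 points.

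**Chi-square against Cochran-Mantel-Haenszel (CMH).** Chi-square is exact; CMH is from 400,000 simulated trials. Strata are equal.

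| Gap (points) | Power, chi-square | Power, CMH | Size at null 50%, chi-square | Size at null 50%, CMH |
|---|---|---|---|---|
| 0 | 86.4% | 85.6% | 4.4% | 4.4% |
| 20 | 86.8% | 86.9% | 4.0% | 4.8% |
| 30 | 87.3% | 88.1% | 3.5% | 5.1% |
| 40 | 88.0% | 89.8% | 2.8% | 5.0% |

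With no gap, CMH loses 86.36 − 85.63 = 0.7 points. At 20 points the two are level.

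**The case against.** The case for leaving the plan alone is substantial, and much of it stands.

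- A reader might infer that pooling always makes the test run below its nominal level and lose power. The document does not support that. It gives neither stratum sizes nor attainment by stratum. With gaps of 0 to 10 points the pooled chi-square test has a size of 4.3% to 5.5% across null rates of 50% and 65%, which is about nominal, and no less power than CMH.
- A reader might also take Fisher's low size as a product of pooling. Most of it is discreteness, the sample size already allows for it, and the stratified exact test is itself at only about 3%.
- Nor is the trial left short of power. Pooled power stays above 80% in every scenario examined and rises with the gap. The plan is consistent in sizing and testing with the same method, and ignoring the strata neither biases the estimate nor inflates the error rate.
- Incomplete blocks and dropout would loosen the balance within strata, so the gains above are probably somewhat optimistic.
- Before May 2014 allocation was also stratified by HbA1c. A test stratified on one factor follows only part of the scheme for those patients.
- The covariate list for the regressions may properly sit in an analysis plan that is not shown, and its absence here is no fault.

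One thing is not answered. The article does name the test for the primary outcome, and that test does not follow the one factor kept throughout. This is a stated choice rather than a detail left to another document.

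**Conclusion.** The mismatch between design and analysis is real, but its consequence is conditional and modest. The pooled test may be used and meets its power target. If initiating/titrating predicts attainment, pooled Fisher gives up about 1, 2 and 3 points of power at gaps of 20, 30 and 40 points, assuming equal strata, 44 per arm, exact balance and a common odds ratio. The loss is smaller with a 25/75 split and essentially nil with no stratum effect. A prognostic effect is plausible, since one group has its whole titration ahead of it and the other already has a dose, but nothing in the article quantifies it. The reason to act is that the stratified exact test was at least as powerful as pooled Fisher in every scenario enumerated, and its size stayed below 5%. This is an improvement in efficiency, not a correction of an invalid analysis.

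**What to change.** Name the primary test of optimal-dose attainment as a two-sided exact conditional test stratified by initiating versus titrating. Include that factor in every logistic and linear model, whatever other baseline characteristics are chosen. Keep the pooled Fisher test as a supporting analysis, which also preserves the link to the sample-size calculation. A Mantel-Haenszel risk difference with its confidence interval would suit as the accompanying estimate. Because the trial is unblinded, the change should be written and dated before outcomes are compared by arm. The article reports that follow-up was still being collected.

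The cost is a sentence or two in the plan and a few lines of code; sample size and data collection are unchanged. With the stratified exact test this is a free improvement. If an asymptotic Cochran-Mantel-Haenszel test is preferred to chi-square, it is a cheap one: about 0.7 points of power are lost if the stratum turns out not to matter, and about 1 to 2 points are gained at gaps of 30 to 40 points.

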### Outcome Measures

The primary outcome will be whether or not a patient reaches his/her optimal insulin glargine dose within 12 weeks of enrolling in the study. Optimal insulin glargine dose is defined as the dose at which the patient has at least one fasting blood glucose value within the range of 80 to 130 mg/dL inclusive, or the maximum dose that can be safely administered to the patient. The research staff will record whether a patient has reached their optimal insulin dose at the time of the patient’s weekly titration phone call (if in the MITI arm) or clinic appointment (if in the usual-care arm).

We hypothesize that the MITI arm will have a greater proportion of patients who reach their optimal insulin dose than the usual-care arm. Other clinical effectiveness outcomes include the time taken to reach optimal dose, the incidence of hypoglycemia, and the change in HbA1c levels between baseline and 3 months.

Feasibility measures include patients’ text message response rate, ability of the diabetes nurse educator to reach patients for insulin titration, and the time spent by the diabetes nurse educator on the intervention.

We will measure patient treatment satisfaction at baseline and 3 months after study enrollment using the Diabetes Treatment Satisfaction Questionnaire. We will use an additional questionnaire—the “change” version of the Diabetes Treatment Satisfaction Questionnaire—to measure the change in the patient’s treatment satisfaction between baseline and 3 months [20]. We will also use a semistructured interview to gather qualitative feedback from patients in the MITI arm. This will be administered when the patient has completed the intervention—by reaching their optimal insulin dose or when 12 weeks elapse.  

We will collect data on the costs of insulin titration to compare the intervention to the established standard of care in the clinic. These outcomes include the time spent by patients traveling to the clinic, time spent in the waiting room prior to appointments, number and duration of insulin titration appointments, patient co-pays, and patient health care utilization (ie, the number of noninsulin-related medical clinic visits made at Bellevue during the 12-week study period).

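### HbA1c change and treatment satisfaction are first compared without baseline adjustment, and the later regression neither commits to the outcome's own baseline nor is named as the main result

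*Protocol article*

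**What the plan says.** Under Outcome Measures, one secondary outcome is "the change in HbA1c levels between baseline and 3 months". For satisfaction the article states: "We will measure patient treatment satisfaction at baseline and 3 months after study enrollment". A separate change form of the questionnaire is also given, "to measure the change in the patient’s treatment satisfaction between baseline and 3 months".

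The Data Analysis section then works in a stated order:

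- Second step: a check of balance between arms in "baseline characteristics (eg, demographic measures and baseline HbA1c levels").
- Third step, the evaluation of intervention effects: a t test or Wilcoxon rank-sum test for "continuous outcomes (eg, change in HbA1c levels, rate of hypoglycemia, scores on the Diabetes Treatment Satisfaction Questionnaire" and others. No covariates enter.
- Fourth step: "we will conduct multiple linear regression analyses for continuous outcomes and multiple logistic regression analyses for categorical outcomes to further evaluate the intervention effects". The covariates of these models are not listed; the article describes the models only as "adjusting for some baseline characteristics and/or their interactions with the treatment assignment". Multiple imputation is placed at this step only.

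Two other sections bear on this. Implementation Challenges reports that stratification by HbA1c (two bands, split at 11%) ended in May 2014 because some patients had no HbA1c on record at enrollment. Recruitment, Randomization, and Retention keeps one stratification factor: starting insulin versus titrating an existing dose.

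**The concern.** The third step comes first and is the one introduced as the evaluation of effect. The fourth is introduced as a further look. Nothing says which result leads, and the covariates of the fourth step are described only as some baseline characteristics, so neither the outcome's own baseline nor the stratum is assured a place in any model.

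Three things are at stake for these two outcomes. The first is precision: the Discussion itself expects limited power, and the plan allows for about 44 evaluable patients per arm. The second is chance imbalance: a change score subtracts baseline but does not remove the dependence of change on baseline, and a 3-month score compared directly does not use baseline at all. The third is choice: with two analyses of undefined priority and open covariates and interactions, in a trial whose research team is not blinded, the leading result could be settled after the data are seen.

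**Working it through.** **The plan's own figure.** Sample Size (Power Analysis) gives 80% versus 50% for the binary primary outcome, a two-sided Fisher exact test at 5%, and at least 80% power. Exact enumeration gives 79.6% power at 43 per arm and 80.2% at 44, so 44 is reproduced. Then 44/0.9 = 48.9, rounded up to 49 per arm, or 98 in total. This figure does not depend on how the continuous outcomes are analysed.

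**Inputs for the check.** n = 44 per arm comes from the article. The document gives no SD or correlation for HbA1c or the satisfaction score. I assume a baseline/follow-up correlation r between 0.3 and 0.7 and, to begin with, equal SDs s at both times.

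**Formulas** (large-sample variance per patient):

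- 3-month score alone: s²
- change score: 2(1 − r)s²
- ANCOVA: (1 − r²)s²

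So ANCOVA/change = (1 − r²)/[2(1 − r)] = (1 + r)/2, and ANCOVA/3-month score = 1 − r². The first ratio fits HbA1c, which is analysed as change. The second fits satisfaction if 3-month scores are compared directly.

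| r | Change score | ANCOVA | ANCOVA/change | ANCOVA/3-month score |
|---|---|---|---|---|
| 0.3 | 1.40 | 0.91 | 0.65 | 0.91 |
| 0.5 | 1.00 | 0.75 | 0.75 | 0.75 |
| 0.7 | 0.60 | 0.51 | 0.85 | 0.51 |

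**In terms of power.** An effect with 80% power in the unadjusted test has power Φ(2.80/√ratio − 1.96) under ANCOVA:

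- against the change score: 93.5%, 89.9% and 86.0% at r = 0.3, 0.5 and 0.7
- against the 3-month score: 83.6%, 89.9% and 97.5%

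**Sensitivity to equal SDs.** With baseline SD equal to k times the follow-up SD, the change-score variance is 1 + k² − 2rk in units of the follow-up variance. The ANCOVA variance stays at 1 − r².

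| r | ANCOVA/change, k = 0.8 | ANCOVA/change, k = 1.2 |
|---|---|---|
| 0.3 | 0.91/1.16 = 0.78 | 0.91/1.72 = 0.53 |
| 0.5 | 0.75/0.84 = 0.89 | 0.75/1.24 = 0.60 |
| 0.7 | 0.51/0.52 = 0.98 | 0.51/0.76 = 0.67 |

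**Chance imbalance.** With equal SDs, a baseline difference d between arms moves the expected change-score contrast by −(1 − r)d and the 3-month contrast by rd. At 44 per arm one standard error of d is √(2/44) = 0.21 SD. At r = 0.5 either contrast moves by about 0.5 × 0.21 = 0.11 SD, in opposite directions. Averaged over randomisations the shift is zero.

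**The case against.** The strongest reply is that the plan already contains the remedy. The fourth step is a linear regression, and baseline HbA1c is the article's own example of a baseline characteristic. Regressing HbA1c change on arm and baseline HbA1c gives the same treatment coefficient as regressing the 3-month value on both. A covariate list for secondary outcomes may well sit in a statistical analysis plan that is not shown. All of this stands, and the absence of a list is not the point. The point is the order that the article does fix: the less efficient comparison evaluates the effect, and the regression follows as a supplement.

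Two stronger readings are tempting, and the document supports neither:

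- **That baseline values are ignored.** They are not. The HbA1c change score uses baseline by subtraction, the change form of the questionnaire asks about change since baseline, and the regression may include baseline HbA1c. What is lacking is a commitment to baseline as a covariate.
- **That the unadjusted tests are biased.** Under randomisation they are unbiased with valid type I error. The shift shown above is conditional on a chance imbalance.

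Two further replies limit the size. HbA1c stratification applied from June 2013 up to May 2014, about 11 of the 19 calendar months of recruitment, so balance on HbA1c was controlled by design for part of the sample. And entry at HbA1c of 8% or more may narrow the baseline spread, which points towards k below 1 and a smaller gain over the change score.

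**Conclusion.** The concern holds as one of efficiency, chance imbalance and unclear priority for two secondary outcomes. Under equal SDs and r from 0.3 to 0.7, the unadjusted change-score variance for HbA1c is about 18% to 54% larger than under ANCOVA (1/0.85 to 1/0.65). The unadjusted 3-month satisfaction variance is about 10% to 96% larger (1/0.91 to 1/0.51). Both r and the equal SDs are assumptions. If the baseline SD is 0.8 of the follow-up SD, the gain over the change score falls to between 22% and 2% of the variance; if it is 1.2 times, the gain is larger. The direction is firm and the size is uncertain.

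A reader might infer that the trial is underpowered or its main conclusion threatened. Neither follows: the primary outcome is binary, its sample size reproduces, and nothing here touches it.

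**What to change.** For HbA1c and the satisfaction score, name the regression already planned as the main analysis:

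- 3-month HbA1c on arm, baseline HbA1c and the initiation/titration stratum.
- 3-month satisfaction score on arm, its baseline score and the same stratum.
- Use the multiple imputation already planned at that step for missing values, including a missing baseline HbA1c.
- Report adjusted mean differences with 95% confidence intervals, and keep the t test or rank-sum test as a sensitivity analysis.
- The change form of the satisfaction questionnaire has no baseline of its own. Leave it as a simple comparison, or adjust it for the stratum only.

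The cost is wording. The baseline measurements are already planned, and neither recruitment nor the sample size changes. The choice should be recorded and dated before outcomes are examined by arm.
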